#### Sample size

3.4.2

Previous risk communication intervention studies were utilized to estimate the sample size. In our previous survey (46), we observed a baseline proportion of healthy lifestyle adherence at approximately 30% among participants with familiar sample characteristics. For the intervention groups, we anticipate a relative increase of at least 50% (47), with an expected difference of 25% between the gain- and loss-framed groups (39). This corresponds to an estimated effect size (W) for Chi-square of 0.20 (48), aligning closely with recommendations from prior studies (38). To achieve a power of 80%, an alpha error rate of 0.05, a standard deviation of 5%, and an estimated effect size (W) of 0.20, a total of 198 participants will be required for our primary outcome, which measures a healthier lifestyle encompassing physical activity, diet, and prevention medication at 3 months. These participants will be evenly distributed into three groups: gain-framed, loss-framed, and no-frame message interventions. However, considering the dropout rate of 20%, a sample size of 240 participants will be required.

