#### Recruitment

3.4.3

A total of 240 participants will be recruited at the chronic disease management clinic of each community between October and November 2023. In order to screen eligibility participants effectively, the research team will collaborate with community clinic staff to review medical records of individuals with hypertension, diabetes, or dyslipidemia. The 10-year CVD absolute risk will be estimated individually using the China-PAR model (Prediction for Atherosclerotic cardiovascular disease Risk) through an online calculator.^1^ Participants whose risk values exceed 5% will be marked as potentially eligible participants. Patients who meet the eligibility criteria will be contacted by the GP to gage their interest in learning more about this research project. Subsequently, proficient study personnel will reach out to the participants via telephone by the investigators within a two-week timeframe to provide detailed information about the study. Eligible participants will be recruited after signed consent is obtained. Each participant will be assigned a unique identification code, such as JA001. The initial character of the code signifies the study site (e.g., J = Jinhua), the subsequent character represents the risk perception group (A = Under-perceived, B = Over-perceived, C = correct-perceived), and the final three numerical digits correspond to the sequence of enrollment. This code will be used for the purpose of randomization.

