#### Primary outcomes

3.7.1

The primary outcome aims to assess two key aspects: (1) CVD prevention behaviors, encompassing healthy physical activity, a balanced diet, and adherence to preventative medication; and (2) CVD absolute risk.

Healthy physical activity will be assessed using the questionnaire of self-reported International Physical Activity Questionnaire-short version (IPAQ) (54). The responses were processed and aggregated using the IPAQ guidelines for Chinese (55). Participants who achieved a minimum of 150 min of moderate-intensity physical activities or 75 min of vigorous-intensity physical activities per week were considered to have fulfilled the criteria for adequate physical activity (56).

Healthy diet will be assessed through healthy diet score based on the updated Chinese Dietary Guideline (57). The assessment included the weekly consumption of six food groups, namely fresh fruit, fresh vegetables, whole grains, fish and other seafood (consumed more than once per week), bean and bean food (consumed at least four times per week), and red meat (consumed less than seven times per week). The response that met the established criteria received a score of 1 for each food group, and the cumulative score was calculated (with a maximum score of 6). The healthy group was defined as individuals with a total score of 4 or higher (58).

Taking preventative medication will be evaluated through medical prescription for stain/lipid lowering, anticoagulants, antihypertension, glucose-lowering medications (59), based on data obtained from the community physician health check system.

The estimation of CVD absolute risk, including both 10-year and lifetime CVD risk, will be performed using the China-PAR equation (50). Participants will be classified into three groups based on the China-PAR cut-off value specified in the Chinese guidelines (56), namely low risk (<5%), moderate risk (5–9.9%) and high risk (≥10%); for lifetime CVD risk: low risk (<32.8%), and high risk (≥32.8%).

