#### Data analysis

3.8.1

Descriptive statistical analysis will be conducted for all measurements. The distributions of categorical baseline variables will be compared using χ^2^ test among the three intervention groups. The difference in continuous variables will be analyzed using either one-way analysis of variance (ANOVA) or a non-parametric rank-sum test. The differential changes in the primary (i.e., healthy behaviors) and secondary (i.e., risk perception) outcomes at T1 and T2, relative to T0, across the three groups will be assessed using generalized estimating equations (GEE) models. GEE methods were applied to estimate model parameters using a binomial distribution for the variance function, a logit link function, and accounting for clustering via an assumed exchangeable working correlation structure (65). The outcomes will be used as dependent variables (one for each model) and, as independent variables, the intervention arms (no-framed, gain-framed, loss-framed message), the factors time (T0, T1, T2), the covariates (risk perception categories) and their corresponding interaction term. The other potential confounders (i.e., variables with baseline imbalances, study sites) will be added as independent variables to adjust GEE model. An exchangeable working correlation structure will be assumed in order to assess the association between factors and outcomes. The statistical significance of each parameter in the model will be analyzed using a Wald test. To account for the potential occurrence of type 1 errors, a Bonferroni correction will be implemented for all GEE models, with a *p*-value threshold of less than 0.003 indicating statistically significant differences (66). The final model’s results will be presented as estimated odds ratio (*OR*) and 95% confidence interval (*CI*) for each significant prognostic variable. We will also conduct the sensitivity analysis to assess the non-response mechanism (67) and an attrition analysis (68) to identify the differential dropout rates and dropout by group interaction on sociodemographic and pretest variables that may pose a threat the equity of the findings (69). Subgroup analysis was performed for cases that did not pass the manipulation check. The principle of “intention to treat (ITT)” will be applied in conducting all primary and secondary outcome analyses. Moreover, the patterns of missingness would be recorded across variables and time points to provide insight into non-random missingness. Statistical significance will be determined by results with *p* < 0.05 in two-sided tests. The analysis will be carried out using SPSS software for MAC (version 26.0) and R software (version 4.3.1).

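### The 80% power is stated for one combined lifestyle outcome that the article never defines, and the medication component is called adherence but measured as prescription

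*Protocol article*

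**What the plan says.** Section 3.4.2 (Sample size) starts from a single proportion, about 30% with a healthy lifestyle, and expects a relative increase of at least 50% in the intervention groups. It converts this to an effect size: "This corresponds to an estimated effect size (W) for Chi-square of 0.20". The remaining settings are given as "To achieve a power of 80%, an alpha error rate of 0.05". The result, 198 before dropout, is for one outcome, "which measures a healthier lifestyle encompassing physical activity, diet, and prevention medication at 3 months".

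Section 3.7.1 (Primary outcomes) names two primary aspects. The first is "CVD prevention behaviors, encompassing healthy physical activity, a balanced diet, and adherence to preventative medication". Physical activity has its own yes/no criterion, and diet has its own cut-off of 4 out of 6. Medication has no cut-off: "Taking preventative medication will be evaluated through medical prescription", with data from the community physicians' system. The second aspect is absolute CVD risk, both 10-year and lifetime.

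Section 3.8.1 (Data analysis) says: "The outcomes will be used as dependent variables (one for each model"). It gives healthy behaviours as the example of a primary outcome, sets a Bonferroni threshold of 0.003 for all GEE models, and later in the same section gives 0.05 as the general significance level. Table 1 labels the medication row as a prescription item, collected at T0, T1 and T2.

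**The concern.** A power statement means something only for a variable that will exist in the data set and be tested at the level assumed. Here the sized outcome is one yes/no lifestyle variable, while the outcome section lists separate behaviours and risk measures and does not say how to get from one to the other. All three criteria met, any one met, or a score cut-off would each give a different variable with a different baseline rate. No rule says which primary outcome must succeed. If the rule is left open, the primary result can be settled after the data are seen, and a null result on any one outcome cannot be read against the stated 80%.

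The medication item raises a second problem. A prescription records what the physician ordered. Messages sent to participants could change whether they take tablets already prescribed, and this variable would not show it. Recruitment works from a "review medical records of individuals with hypertension, diabetes, or dyslipidemia", so a sizeable share may already hold a prescription at T0. The article gives no figure, so how much room the variable has to change is unknown.

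**Working it through.** **Inputs.** From section 3.4.2: w = 0.20, alpha = 0.05, power = 80%, three equal arms, 198 evaluable. From section 3.8.1: threshold 0.003 for GEE models. Degrees of freedom are not stated.

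**Reproducing 198.** For a chi-square test the noncentrality is N × w². Power is the probability that a noncentral chi-square exceeds the critical value.

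- 1 df: 80% power needs N = 197, or 198 as the next multiple of 3. At N = 198 the noncentrality is 198 × 0.04 = 7.92 and power is 80.4%. As a check, √7.92 = 2.814, and 2.814 − 1.960 = 0.854 gives about 80%.
- 2 df, the natural test for three arms by yes/no: N = 241. At 198, power is 71.3%.

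At the stated w, 198 is therefore one 1-df test of one binary outcome at 0.05. (Rates of 30%, 45% and 20% would give w = 0.22, and a 2-df test then also needs 198. That is not the stated w, and it is still one test of one outcome at 0.05.) Nothing in the figure allows for several primary outcomes.

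**If the outcomes are tested separately.** Assumptions: w = 0.20 for each outcome, each treated as binary, Bonferroni split, 198 evaluable.

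| Setting | Alpha per test | Power at 198, 1 df | Power at 198, 2 df | N for 80%, 1 df | N for 80%, 2 df |
|---|---|---|---|---|---|
| As planned, one outcome | 0.05 | 80% | 71% | 197 | 241 |
| Three behaviours | 0.05/3 = 0.0167 | 66% | 55% | 262 | 314 |
| Three behaviours plus one CVD risk measure | 0.05/4 = 0.0125 | 62% | 51% | 279 | 333 |
| The article's GEE threshold | 0.003 | 44% | 33% | 363 | 424 |

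These are chi-square illustrations, not the power of the planned GEE models.

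**Dependence of the 30% on the missing rule.** Assume three independent behaviours with equal rates. If 30% means all three are met, each rate is 0.30^(1/3) = 67%. If it means at least one is met, each rate is 1 − 0.70^(1/3) = 11%. Both assumptions are for illustration only, but they show that the planning rate cannot be carried over to the components without the rule.

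**Medication.** Set side by side, section 3.7.1 first names adherence, then taking, then prescription as the source. Table 1 has prescription only. No section gives a pill count, refill record, self-report or other measure of intake.

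**The case against.** The strongest defence is that this is a condensed article. The full protocol or SAP may hold the combining rule, and the 30% comes from the team's own survey, where a definition presumably exists. Section 3.8.1 does not list its models, and its example of healthy behaviours does not exclude a combined variable. That stands in part: separate modelling of the three behaviours is an inference from one model per outcome together with the outcome list, and the claim must be limited to what this document defines. But the article gives the component thresholds in detail, down to the diet cut-off and the risk bands, and still does not define the one variable it sizes. It also adds an unsized second primary aspect. That is a mismatch between sections, not mere brevity.

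Three stronger readings are tempting and are not supported.

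- A reader might infer a 23% chance of a false claim from five primary tests at 0.05 (1 − 0.95^5 = 0.226, if independent). The article sets 0.003 for all GEE models, at which five independent tests give 1 − 0.997^5 = 1.5%. The later general mention of 0.05 conflicts with this, but the document does not establish 23% as the plan's error rate.
- A reader might infer that the planned effect is impossible, because 67% × 1.5 is about 100%. The 50% increase is attached to the 30% lifestyle rate, giving 45%. Under the same assumptions each behaviour would move from 67% to 0.45^(1/3) = 77%, which is possible.
- A reader might infer that no medication effect could appear at all. A participant who becomes willing to start treatment could receive a new prescription, and that would be recorded. What the variable cannot show is whether prescribed medication is taken.

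It is also fair that Table 1 already uses the prescription label and collects T0 data, so this part is mainly an inconsistency of wording. Whether CVD risk should remain primary is a design choice that the sponsor may keep.

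**Conclusion.** The point holds in this form: the stated 80% power belongs to a single binary lifestyle outcome tested once at 0.05, and the document defines no such outcome. CVD risk is declared primary without being sized. If each behaviour had w = 0.20, 198 participants would give about 66% power with 1 df (55% with 2 df) at 0.05/3, and about 44% (33%) at the stated 0.003. These figures rest on an equal w for every outcome, which the article does not support or rule out. The figure of 198 is not itself an arithmetic error. Separately, section 3.7.1 names adherence but measures prescription, so an adherence conclusion would go beyond the data. Both matters should be corrected before analysis.

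**What to change.** 1. Name the powered primary variable as the binary behaviour outcome at T2, formed by the same rule that produced the 30% planning rate. Write that rule into section 3.7.1, including the missing yes/no criterion for medication, and state that the 80% power applies to this variable only.
2. If the behaviours and CVD risk are instead to be tested separately as primary outcomes, restate the power for each, CVD risk included, at the significance threshold that will actually be used.
3. Rename the medication component as preventive medication prescribed, report its T0 prevalence by arm, and draw no conclusion about adherence from it.

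The cost is a change of wording in sections 3.4.2, 3.7.1 and 3.8.1. The data are already scheduled in Table 1. The price is fewer headline claims under the first option, or a less favourable stated power under the second.

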#### Recruitment

3.4.3

A total of 240 participants will be recruited at the chronic disease management clinic of each community between October and November 2023. In order to screen eligibility participants effectively, the research team will collaborate with community clinic staff to review medical records of individuals with hypertension, diabetes, or dyslipidemia. The 10-year CVD absolute risk will be estimated individually using the China-PAR model (Prediction for Atherosclerotic cardiovascular disease Risk) through an online calculator.^1^ Participants whose risk values exceed 5% will be marked as potentially eligible participants. Patients who meet the eligibility criteria will be contacted by the GP to gage their interest in learning more about this research project. Subsequently, proficient study personnel will reach out to the participants via telephone by the investigators within a two-week timeframe to provide detailed information about the study. Eligible participants will be recruited after signed consent is obtained. Each participant will be assigned a unique identification code, such as JA001. The initial character of the code signifies the study site (e.g., J = Jinhua), the subsequent character represents the risk perception group (A = Under-perceived, B = Over-perceived, C = correct-perceived), and the final three numerical digits correspond to the sequence of enrollment. This code will be used for the purpose of randomization.

#### Risk perception categories

3.4.4

The risk perception categories (correct perceived, under-perceived or over-perceived CVD risk) are determined by comparing risk perception level (CVD risk perception assessed using ABCD-C) (49) and 10-year CVD risk level (10-year CVD absolute risk calculated using China-PAR) (50, 51) with cross-tabulation using the baseline data, and the details were described in our previous study (19).

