### Study design

3.1

A multi-center 3 × 3 randomized factorial, observer-blinded experimental design was conducted to evaluate the effect of gain-, loss-versus no frame message and under-, over- versus correct risk perception. This trial will be implemented on the basis of National Basic Public Health Service Program (45) and Zhejiang Province Basic Public Service standards (2021 edition). Those includes essential health services for all citizens and chronic health management for hypertensions and diabetes, such as having a free physical examination opportunity once a year, and the electronic physical examination recorded in the community health care system, so that general practitioners (GP) could provide continuous health management services. This study was approved by the Human Research Ethics Committee of the second affiliated Hospital of Zhejiang University school of Medicine (No.2023-0877). It was registered and approved by China Clinical Trials Center (ChiCTR2300076337). We followed the SPIRIT guidelines, and all participants will be followed up for 3 months (Figure 1).

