#### Eligibility criteria

3.4.1

Inclusion criteria: Aged 20–80 years old; permanent residence; accessible for reliable CVD risk calculation indicators from health examination records (waistline, blood pressure, total cholesterol, high density lipoprotein cholesterol measured in last 6 months); a 10-year risk of absolute CVD risk (based on China-PAR model) of at least 5%; had access to a telephone to receive picture or video message from WeChat; normal visual acuity and hearing (with correction); speaking with Mandarin; be able to adhere to all study procedures.Exclusion criteria: Experienced incident CVD or stroke before; experienced severe anxiety; engagement in concurrent participation in another health research study; current or planned pregnancy during the study period; restricted physical activity due to other medical conditions; and ongoing treatment for severe disease or terminal medical condition.

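### The framing-by-perception test has no framing-by-baseline-risk term, although perception category is built partly from baseline risk, and covariates other than site are chosen by observed imbalance between arms

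*Protocol article*

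**What the plan says.** - **Entry.** Section 3.4.1 requires "a 10-year risk of absolute CVD risk (based on China-PAR model) of at least 5" per cent.
- **Calculated levels.** Section 3.7.1 sets 10-year levels as "low risk (<5%), moderate risk (5–9.9%) and high risk (≥10" per cent), so only the upper two levels can enrol.
- **Perception category.** Section 3.4.4 says the categories "are determined by comparing risk perception level (CVD risk perception assessed using ABCD-C") with the "10-year CVD risk level (10-year CVD absolute risk calculated using China-PAR"). This is done "with cross-tabulation using the baseline data, and the details were described in our previous study". The number of perceived levels and their cut-offs are not in the article.
- **Design label.** Section 3.1 says that a 3 × 3 "randomized factorial, observer-blinded experimental design was conducted". The abstract and section 3.5 make clear that only the message arm is randomised.
- **Model.** Section 3.8.1 names arm, time, perception category and their interaction. Further adjustment follows a rule: "The other potential confounders (i.e., variables with baseline imbalances, study sites) will be added as independent variables to adjust GEE model". The baseline comparisons described there are between the three arms. Baseline China-PAR risk and a framing-by-risk term are not named.

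**The concern.** The aim in section 2 is the best message for each perception category, and the Discussion plans software that matches message to category. The Discussion also presents accuracy of perception, as distinct from perceived risk alone, as the gap to be filled. That claim requires accuracy to be separated from actual risk, yet the category is computed from actual risk.

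Framing could plausibly act differently by calculated risk. In the example modules of sections 3.6.2 and 3.6.3, the framed content is built from the person's own calculated risk and its gap to an ideal level (6.3% against 4.4%). If the effect of a frame depends on calculated risk, part of that dependence will appear as a framing-by-perception pattern, and the planned model has no term to tell the two apart.

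The covariate rule is a separate weakness. Selecting by imbalance between arms ignores prognostic strength and makes the final model depend on chance. It also looks in the wrong direction for this problem: randomisation tends to balance risk between arms, whereas the difference here lies between perception categories.

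**Working it through.** **Plan's own figure.** Section 3.4.2 gives no figure for the perception interaction, only a total of 198 for w = 0.20, 80% power and alpha 0.05. A 1-df chi-square with noncentrality N·w² needs N = 197; the next multiple of three is 198. The figure reproduces on that basis and is used below only as the analysed sample size.

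**Step 1: which categories can occur.** Assumption: three perceived levels matched to the China-PAR levels.

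| Calculated level | Perceived low | Perceived moderate | Perceived high |
|---|---|---|---|
| Moderate (5–9.9%) | under | correct | over |
| High (≥10%) | under | under | correct |

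No high-risk person can be over-perceived.

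**Step 2: share of high-risk people in each category.** Let h be the high-risk share, and let q1, q2, q3 be the probabilities of perceiving low, moderate and high, independent of calculated level (assumption).

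- Under: h(q1+q2) / [(1−h)q1 + h(q1+q2)]
- Correct: h·q3 / [(1−h)q2 + h·q3]
- Over: 0

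With h = 0.5 and equal q:

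- Under: 0.333/0.500 = 0.67
- Correct: 0.167/0.333 = 0.50
- Over: 0, and this group is 0.5 × 1/3 = 17% of the sample

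**Step 3: apparent framing effect.** Take the 25-point framing difference of section 3.4.2, place all of it in high-risk people, and give perception no role. The apparent effect is 25 × the high-risk share. With h = 0.5 and equal q this is 16.7 points (under), 12.5 (correct) and 0 (over).

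For h = 0.3, 0.5 and 0.7 and perceived mixes (1/3, 1/3, 1/3), (0.5, 0.3, 0.2) and (0.2, 0.3, 0.5):

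| Category | Lowest | Highest |
|---|---|---|
| Under | 25 × 0.24/0.59 = 10.2 | 25 × 0.35/0.41 = 21.3 |
| Correct | 25 × 0.06/0.27 = 5.6 | 25 × 0.35/0.44 = 19.9 |
| Over | 0 | 0 |

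**Step 4: rejection rate of the interaction test.** Simulation settings: 1,000 runs per setting, baseline rate 30%, equal q, one time point, and a linear-probability F test on the four framing-by-perception terms at 0.05. This simplifies the planned logit GEE. The true model has a 25-point effect of one frame in high-risk people only. Ranges run over h = 0.3, 0.5 and 0.7.

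| Model | N = 198 | N = 2000 |
|---|---|---|
| No risk term | 0.067–0.085 | 0.33–0.55 |
| Risk as main effect only | 0.067–0.088 | 0.35–0.56 |
| Risk and risk × arm | 0.052–0.055 | 0.038–0.061 |

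With no framing-by-risk effect, the model without a risk term rejects in 0.044–0.060 of runs. Only the risk × arm term removes the excess.

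**Step 5: the imbalance rule.** Section 3.7 lists 11 baseline items if the three diagnoses are counted separately. If imbalance means p < 0.05 and the tests are independent (both assumptions), at least one is flagged by chance in 1 − 0.95¹¹ = 43% of sound randomisations.

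**The case against.** - **The structural premise rests on details not shown.** This stands. The cut-offs are left to an earlier study. The premise fails if the scheme allows a perceived level above the highest calculated level, so it must be stated conditionally.
- **Arms are randomised, so each within-category contrast is valid for that category as enrolled.** This stands. For choosing a message by category in people at 5% or more, such a contrast is usable even if the category partly encodes risk. A reader might infer that framing-by-perception is wholly confounded or that the framing main effect is biased. Neither is supported: moderate-risk people can occur in all three categories, and the main effect is untouched. What remains is attribution to perception.
- **The covariate rule does not cause the attribution problem.** This also stands. Nor does leaving risk out as a main effect, since adding it changes almost nothing in step 4. The two weaknesses should be kept apart. Site is already in the model whatever its balance.
- **The article describes a pilot, and an analysis plan may exist.** A full covariate list and sensitivity analyses are commonly left to that plan. But the imbalance rule is stated here, and it is the stated rule that is poor.
- **The factorial label is loose rather than misleading**, because the article itself says what is randomised. A wording change is enough.

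**Conclusion.** The point holds in a limited form. As written, the analysis cannot distinguish a framing effect that depends on accuracy of perception from one that depends on calculated risk, and its covariate rule would not reveal the difference.

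Under matched three-level categories, perception independent of calculated level, 30–70% at high risk and a 25-point effect confined to high-risk people, the spurious pattern is 0 points in over-perceived, about 6–20 in correctly-perceived and 10–21 in under-perceived people. Confining the whole effect to high-risk people is an extreme case; a weaker dependence on risk gives a weaker pattern.

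A reader might infer that the trial is likely to declare a false match. The figures do not support that. At N = 198 the false-positive rate is about 7–9% against 5%. The stricter 0.003 threshold that section 3.8.1 sets for the GEE models would lower the absolute rate further, though that was not simulated. The harm lies in the interpretation of category-specific estimates. The correction is cheap and worth making.

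**What to change.** 1. Replace imbalance-based selection with covariates prespecified for prognostic value: site (already named), age, sex, education and, for the behaviour outcomes, baseline China-PAR risk.
2. For the behaviour outcomes, prespecify a sensitivity analysis with baseline risk × arm (× time) next to perception × arm.
3. Report framing-by-perception within the 5–9.9% stratum as supportive. Under matched levels it is the only stratum where all three categories can occur.
4. Do not enter baseline risk as a covariate in the model where absolute risk is the outcome and T0 is a level of time; the T0 outcome would be regressed on itself.
5. Describe the design as a three-arm randomised trial with perception category as a baseline effect modifier.

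**Cost.** No new data are needed. With a single risk term, the full risk × arm × time version adds 1 + 2 + 2 + 4 = 9 parameters, and intervals on the interaction widen. Cells in the moderate stratum are small: if half of 240 are moderate risk and perceived levels are equally likely, 120/9 is about 13 per cell before dropout. Items 2 and 3 should therefore stay sensitivity and supportive analyses.
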